## Abstract

**Rationale:**

Long-acting muscarinic antagonists (LAMAs) reduce the risk of acute exacerbations of chronic obstructive pulmonary disease (AECOPD), usually taken once daily in the morning. However, the circadian activity of autonomic regulation suggests that the highest need for anticholinergic therapy may be in the late night/early morning. This is supported by evidence that AECOPD most often begins in the morning. Furthermore, the trough spirometry effect of LAMA is lower than the peak effect, which further argues that evening dosing may be more optimal than morning dosing. This trial aims to determine whether evening administration of LAMA reduces hospitalization-requiring AECOPD or death from all causes within 1 year as compared to morning administration of the same LAMA.

**Methods:**

Randomized controlled open-label trial. Persons aged 30 years or older with a once-daily LAMA prescription and a confirmed COPD diagnosis were recruited. Participants were randomized in a 1:1 ratio to either morning or evening LAMA administration. Complete follow-up for the primary outcome, hospitalization-requiring AECOPD, or death from all causes within 1 year was captured from the Danish National Health Register, as were patient-reported outcome assessments at 6 and 12 months.

**Results:**

A total of 10,013 participants were randomized, and the recruitment process started on 9 March 2023. Secondary outcomes include (i) moderate COPD exacerbations; (ii) all-cause hospitalization; (iii) ICU admission; (iv) need for non-invasive ventilation; and (v) all-cause mortality, among others. All outcomes will be evaluated 12 months after recruitment.

**Clinical trial registration:**ClinicalTrials.gov, NCT05563675.

## Introduction

### Background and rationale

One of the most serious complications of chronic obstructive pulmonary disease (COPD) is acute exacerbation (AECOPD). On average, each COPD patient experiences 0.5–3.5 acute exacerbations per year, which is an important reason for hospitalization, disease progression, and mortality as well as a decline in health status and lung function (1, 2). Treatment with a long-acting muscarinic antagonist (LAMA) reduces dyspnea and the risk of exacerbations in patients with COPD by binding to muscarinic receptors in bronchial smooth musculature and thus inhibiting cholinergic bronchial constriction. LAMAs are given as inhalation therapy once daily (most often) or twice daily (3). Most COPD patients experience their worst symptoms and experience exacerbations in the early morning hours, before getting out of bed (4). This might be explained by the physiological diurnal changes in the activity of the parasympathetic homeostasis system, which is most active at night to improve digestion and other secretions (5). Correspondingly, the activity of the sympathetic system is physiologically suppressed at night, and stimulation of β-2 receptors is thus also low (and opposite for M-3 receptors). The balance of sympathetic-parasympathetic tone is shifted significantly toward the latter. Most available LAMA treatments are dosed once daily in the morning. Thus, for a COPD patient, being at a trough level of LAMA (which antagonizes the parasympathetic system) at late night/early morning, may carry a hazard for the patient. Studies have found that lung function measured as a forced expiratory volume in 1 s (FEV1) improvement peaks approximately 2 h after LAMA administration and that FEV1 is still significantly improved at 7 h post-treatment but decreases toward the trough level of the LAMA (6). However, as a corollary to the above, when the medicine is probably most needed (02.00 a.m.–07.00 a.m.), the effect is at its lowest level, which may not be desirable, since a low effect of the most important preventive medicine against AECOPD at this time may lead to more exacerbations. Evening administration, on the contrary, would lead to a greater and more certain effect regarding bronchodilation and reduced secretion in the early morning hours, and a maximum effect should be expected during the entire night.

### Objectives

The main objective of this intervention and research protocol is to determine whether evening administration of LAMA, as opposed to morning administration, is superior for the occurrence of hospitalization-requiring AECOPD or death from all causes. The intervention will have the following secondary objectives: (1) moderate COPD exacerbations, (2) all-cause hospitalization, (3) intensive care unit (ICU) admission, (4) need for non-invasive ventilation, (5) all-cause mortality, (6) Short-Acting Beta-Agonist (SABA) use / pick up rate, and exploratory endpoints (1) change in COPD Assessment Test (CAT) score, (2) change in Medical Research Council (MRC) score, and (3) change in the “soundly sleeping” parameter of CAT.

### Trial design

The study is a pragmatic, registry-based, open-label, randomized controlled trial combining the utilization of the Danish nationwide health registries and the official Danish electronic letter system (Digital Post/e-Boks) into an innovative, decentralized trial requiring no study visits from participants. The trial will include patients receiving LAMA treatment that will be randomized 1:1 to either LAMA administration in the evening or the morning for 12 months.

## Methods: participants, interventions, and outcomes

### Study setting

This study will be conducted by the Chronic Obstructive Pulmonary Disease Trial Network (COP:TRIN) at the Section of Respiratory Medicine, Copenhagen University Hospital – Herlev and Gentofte, Copenhagen, Denmark. This group will be responsible for all processes in the study, including recruitment, inclusion, randomization, follow-up, and communication with participants. Registry data will be obtained through the Danish Health Data Authority and accessed through an encrypted remote-access server environment. The study will identify potential participants across Denmark through nationwide health registries, and the electronic letter system (Digital Post/e-Boks) will be used for sending recruitment letters and communicating with patients. The trial recruits and allocates patients electronically, and follow-up consists of electronic questionnaires, while endpoints are assessed using data from national registries. Therefore, there is no list of specific study sites/clinics/hospitals.

### Eligibility criteria

Inclusion criteria:

Age > 30 years.Current treatment with LAMA once daily (as recorded in the Danish National Prescription Registry and confirmed by the participant via questionnaire).Confirmed COPD diagnosis.

Exclusion criteria:

Patients who decline to participate.

### Who will obtain informed consent?

We have obtained a waiver from the regional science ethics board for informed consent since the medication and dose will not be changed. The science ethics board argues that the intervention lies beyond the scope of the science ethics legislation in Denmark.

However, only those who provided consent to the written information, and who reported having COPD, are included. We have obtained approval from the Data Protection Agency (P-2022-432) on 1 July 2022.

### Additional consent provisions for collection and use of participant data and biological specimens

No biological specimens will be obtained. Regarding informed consent, see previous section.

## Interventions

### Explanation for the choice of comparators

Patients will be randomized 1:1 to one of the two treatment strategies by computer-generated allocation to either:

LAMA administration in the morning (control).LAMA administration in the evening (intervention).

These treatment strategies have been chosen because morning administration is the most conventional, while evening administration will be investigated to determine if it is superior with respect to the occurrence of hospitalization-requiring AECOPD or death from all causes within 12 months, along with several secondary and exploratory outcomes, as outlined in Table 1.

**Table 1 tab1:** Primary endpoint definition.

Endpoint	ICD-10 codes	Inpatient/outpatient/minimum required length of stay/other criteria
Hospitalization-requiring AECOPD or death from all causes	Hospitalizations: DJ440, DJ441	For hospitalizations: Type A Diagnosis (primary discharge diagnosis). Inpatient and length of stay ≥24 h, or emergency room visits

The time frame is ≥1 day after randomization until the end of the study (12 months). COPD, chronic obstructive pulmonary disease.

### Intervention description

Participants randomized to LAMA administration [with or without the combination of inhaled corticosteroids (ICSs) and/or long-acting beta-2-agonists (LABAs)] in the evening will be instructed to take their LAMA-containing inhalation between 8 p.m. and 2 a.m.

Participants randomized to LAMA administration (with or without the combination of ICS and/or LABA) in the morning will be instructed to take their LAMA as usual in the morning between 6 and 12 a.m.

### Criteria for discontinuing or modifying allocated interventions

Investigators may pause or interrupt the intervention at any given time in case of medical reasoning, safety risks, or requirements from the authorities.

Furthermore, participating patients can withdraw from the intervention or the entire trial at any given time without providing a reason (Figure 1).

**Figure 1 fig1:**
[figure not shown]
Clinical trial flowchart.

### Strategies to improve adherence to interventions

Reminders on LAMA administration time will be sent to participants every month until the first questionnaire (6 months), and then at 9 months.

### Relevant concomitant care permitted or prohibited during the trial

N/A: no specific concomitant care or interventions are prohibited during the trial.

### Provisions for post-trial care

The trial is covered by the patient compensation scheme if, contrary to expectation, damages occur during the trial and by inclusion.

### Outcomes

The primary efficacy endpoint is the occurrence of hospitalization requiring AECOPD or death from all causes within 12 months. Secondary efficacy endpoints included (i) moderate COPD exacerbations; (ii) all-cause hospitalization; (iii) ICU admission; (iv) need for non-invasive ventilation; (v) all-cause mortality; (vi) SABA use/pick-up rate; and exploratory endpoints (i) relation between adherence and AECOPD hospitalization, (ii) change in CAT score, (iii) change in MRC score, and (iv) change in “soundly sleeping” parameter of CAT.

The details on the primary and secondary outcomes of the study can be seen in Tables 1, 2, and exploratory outcomes in Table 3.

**Table 2 tab2:** Secondary and exploratory endpoint definition.

Endpoint	ICD-10/ATC codes	Inpatient/outpatient/minimum required length of stay/other criteria
Moderate COPD exacerbations	Prednisolone: H02AB06 or Antibiotics: J01CA04, J01AA02, J01CR02, J01MA14	Excluding hospitalizations and emergency room visits: DJ441 (A)
Hospitalization (all-cause)		Inpatient, length of stay ≥24 h
Hospitalization in ICU (all-cause)		Inpatient, ICU, length of stay ≥24 h
Need for NIV	BGDA1	A or B
Mortality (all-cause)		Participant registered as dead in the CPR register.
SABA use/pick-up rate	R03AC02, R03CC02, R03AC03	Danish National Prescription Registry
Change in CAT score	Questionnaire	At 6 and 12 months
Change in MRC score	Questionnaire	At 6 and 12 months

The time frame is ≥1 day after randomization until the end of the study (12 months from randomization) for all outcomes. A = primary discharge diagnosis and B = secondary discharge diagnosis. COPD, chronic obstructive pulmonary disease; ICU, intensive care unit; NIV, non-invasive ventilation; CPR, Central (National) Person Registry; SABA, short-acting beta-2 agonists; CAT, COPD assessment test.

**Table 3 tab3:** Exploratory endpoint definition.

Endpoint	Data source or ICD-10 codes	Inpatient/outpatient/minimum required length of stay/other criteria
Relation between adherence and hospitalization-requiring AECOPD	Questionnaire, DJ440, DJ441	For hospitalizations: Type A diagnosis (primary discharge diagnosis). Inpatient and length of stay ≥24 h, or emergency room visits. Deaths excluded.
Change in CAT score	Questionnaire	At 6 and 12 months
Change in MRC score	Questionnaire	At 6 and 12 months
Change in CAT “soundly sleeping” parameter	Questionnaire	At 6 and 12 months

A = primary discharge diagnosis. CAT, chronic obstructive pulmonary disease assessment test; MRC, Medical Research Council score.

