### Sample size

In Denmark, approximately 400,000 people are assumed to have COPD; however, approximately a quarter of them have not been diagnosed yet. We have data showing that 178,000 citizens have collected LAMA medication within the last 6 months. At the same time, we know that every year, there are approximately 20,000 admissions with AECOPD (severe AECOPD) and 6,000 deaths in patients with COPD. Assuming 50% of the AECOPD admissions are either unique or preceding a death, there are 16,000 annual events corresponding to our primary outcome. Thus, the annual risk of a primary outcome is approx. 16,000/178,000 = 8.9%. We hypothesize that evening LAMA administration will reduce the relative risk of the primary outcome by 25%, corresponding to a 2.2% absolute risk reduction. Assuming 84.4% uniformly distributed adherence to the intervention (= approximately 1 in 6 does not adhere), this corresponds to a relative risk reduction of 21.3% = 1.9% absolute risk reduction (average effect among all) in the ITT population. Alpha and power (1-beta) are set at 0.05 (two-sided) and 0.8, respectively. This leads to a needed sample size of 6,662 (3,331 + 3,331).

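### The moderate-exacerbation endpoint excludes only DJ441 contacts, so a drug course tied to a DJ440 contact can make one episode count as both severe and moderate

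*Protocol article*

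**What the plan says.** Three tables in the protocol article bear on this point.

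- **Table 1** (section on the choice of comparators) gives the codes for the hospital part of the primary endpoint as "Hospitalizations: DJ440, DJ441". The code must be the primary discharge diagnosis (type A), and the contact rule is "Inpatient and length of stay ≥24 h, or emergency room visits".
- **Table 2** (section Outcomes) defines moderate exacerbations by dispensed drugs: "Prednisolone: H02AB06 or Antibiotics: J01CA04, J01AA02, J01CR02, J01MA14". The last column adds the restriction "Excluding hospitalizations and emergency room visits: DJ441 (A"); its footnote says that A means primary discharge diagnosis.
- **Table 3** (section Outcomes) defines the exploratory endpoint on adherence and hospitalization-requiring AECOPD from "Questionnaire, DJ440, DJ441", with the same type A and contact rule as Table 1.

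The Sample size section treats an admission for AECOPD as the severe grade: "20,000 admissions with AECOPD (severe AECOPD"). No other section adds DJ440 to the Table 2 exclusion or explains its absence.

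**The concern.** The restriction in Table 2 can have only one purpose: to keep exacerbations treated in hospital or in an emergency room out of the moderate category. It does so for DJ441 and leaves DJ440 open, although Tables 1 and 3 treat both codes as severe events.

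Two things are at stake. First, one episode can be graded twice, as severe in the primary endpoint and as moderate in the first-listed secondary endpoint. Second, if evening dosing changes the number of DJ440 events, the drug courses tied to those events move the moderate endpoint in the same direction. Some of the apparent effect on moderate exacerbations would then be the severe-event effect counted again.

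The exact code lists matter in this trial. It is open-label, and its section on blinding relies on prespecified registry definitions to limit bias. The interim-analysis section also gives the wish for adequate power on the secondary endpoints as its reason for not stopping early for efficacy.

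**Working it through.** **Step 1. Compare the codes.**

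| Endpoint | Codes | Source |
|---|---|---|
| Severe AECOPD (primary) | DJ440, DJ441, type A | Table 1 |
| Hospitalization-requiring AECOPD (exploratory) | DJ440, DJ441, type A | Table 3 |
| Contacts excluded from moderate exacerbations | DJ441, type A | Table 2 |

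Severe set minus excluded set: {DJ440, DJ441} − {DJ441} = {DJ440}.

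**Step 2. Follow one episode through the rules.** A participant has a stay of at least 24 h, or an emergency room visit, with DJ440 as primary discharge diagnosis, and collects prednisolone or a listed antibiotic for that episode.

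- Table 1: a primary event.
- Table 2, drug criterion: met.
- Table 2, exclusion: not triggered, because the contact is not coded DJ441.
- Result: the episode is both severe and moderate.

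With DJ441 in place of DJ440, the exclusion applies and the episode is severe only. Two episodes that Table 1 treats alike are handled differently in Table 2. This holds whether the exclusion is read as removing the linked drug course or the participant, since DJ440 is outside it either way.

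**Step 3. How large could it be?** The article prints no figure for this overlap, so there is none to reproduce. A rough ceiling can be built from the Sample size section:

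- AECOPD admissions per year: 20,000. Share assumed there to be unique or to precede a death: 50%. So 0.5 × 20,000 = 10,000. Adding the 6,000 deaths gives the plan's 16,000 events, and 16,000/178,000 = 0.0899 (the article has "16,000/178,000 = 8.9" per cent).
- Severe-admission part alone: 10,000/178,000 = 0.0562, or 5.6%.
- DJ440 share: not given. **Assumption:** 20% to 50%.
- 0.0562 × 0.20 = 0.011 and 0.0562 × 0.50 = 0.028.
- Times 10,013 randomized: about 113 to 281 participants.

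This range assumes that every participant with a DJ440 admission also has a linked qualifying pick-up. It also applies a national planning count of admissions to the trial population, and that count does not mention emergency visits.

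**Step 4. Does it reach the sample size?** The moderate endpoint does not enter that calculation. With p1 = 16,000/178,000 = 0.0899, a relative reduction of 0.25 × 0.844 = 0.211 and p2 = 0.0899 × (1 − 0.211) = 0.0709, two-sided alpha 0.05, power 0.80, 1:1 allocation, pooled variance and continuity correction, the total is 6,662, the stated figure. Only composite-event inputs are used, so changing the Table 2 exclusion leaves it as it is.

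**The case against.** **The size is unknown and may be small.** This stands. The 20–50% share has no basis in the article, and no pick-up fraction is available. The Statistical methods section also applies fractions and relative risks to binomial secondary outcomes. If moderate exacerbation is analysed as yes or no, a leaked course changes a participant's status only when that participant has no other qualifying course in the 12 months.

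**Secondary endpoints need not be independent of the primary.** This is also true. All-cause mortality is itself a component of the primary endpoint, and the article nowhere claims independence. But moderate exacerbation is the endpoint for which Table 2 sets out to separate the two grades, and the separation is incomplete by the article's own codes.

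**The full protocol or SAP may settle it.** The point is not about missing detail. The article prints explicit codes in three tables, and one disagrees with the other two.

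**Stronger readings that a reader might infer, and why the documents do not support them:**

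- *DJ440 admissions themselves count as moderate.* They do not. Table 2 requires a listed drug code, so only a drug course tied to such a contact can pass through.
- *All-cause hospitalization is wrongly defined because it omits the emergency visits that the primary endpoint counts.* Table 2 has "Inpatient, length of stay ≥24 h", a legitimate definition, and nothing in the article requires this endpoint to contain every AECOPD contact. Adding emergency visits for any cause would change what it measures.
- *The 24 h minimum loses early deaths.* Such deaths still count in the primary endpoint and in all-cause mortality. Only the secondary hospitalization and ICU counts leave out those short stays, which is a matter of preference.

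**Conclusion.** The inconsistency is real and follows from the tables alone: Table 2 excludes DJ441 (A) contacts, while Tables 1 and 3 define the severe event by DJ440 or DJ441. Followed as written, the rule lets a prednisolone or antibiotic course tied to a DJ440 contact count as a moderate exacerbation alongside the primary event. It is more than a clerical slip, because programming the table literally would misclassify events in the first-listed secondary endpoint.

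The size of the overlap cannot be computed from the documents. The figure of about 110–280 of 10,013 participants is at most a hypothetical upper bound, conditional on an assumed 20–50% DJ440 share, the plan's national admission figures and a linked pick-up for every such participant. It should not be read as an expected count. Nor should a reader infer that the main result is compromised: the primary endpoint, its test and the sample size of 6,662 do not use the moderate-exacerbation definition.

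**What to change.** In Table 2, change the exclusion for moderate COPD exacerbations to hospitalizations and emergency room visits with DJ440 or DJ441 (A), applied to drug courses linked to that contact. Make the same change in the registry code, and record it as a dated amendment before outcome data are analysed, so that it cannot be taken for a post hoc redefinition.

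The cost is one table cell and the matching line of code. No new data are needed, because clinical endpoints already come from the national registries. The one downside is slightly fewer moderate events. The all-cause hospitalization definition and the 24 h minimum need no change on this account.

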## Statistical methods

### Statistical methods for primary and secondary outcomes

The primary and all secondary outcomes will be analyzed using the intention-to-treat (ITT) approach, which encompasses the entire cohort of randomized participants in the study. Additionally, per-protocol analyses will be conducted for patients taking inhalation medication 6–7 days per week at the allocated administration time for the full duration of the study, along with modified ITT (mITT) analyses for those who have taken less than 6 days or more than 2 days per week for any amount of time. These analyses will be performed on both the primary and all secondary outcomes, providing a comprehensive evaluation of the study’s results.

The primary outcome (hospitalization-requiring AECOPD or death from all causes within 12) will be presented as a fraction with percentage and relative risk with a 95% confidence interval. The groups will be compared using a two-sided binomial test. The same principles will be applied to secondary binomial outcomes. For the SABA pick-up rate, the incidence rate and ratios will be calculated and presented (including 95% confidence intervals) and compared using the chi-squared test. Changes in CAT and MRC (respectively) will be reported as median differences with IQR and compared within and between groups with a paired two-sided Wilcoxon signed-rank test and an unpaired two-sided Wilcoxon rank-sum test. A subgroup analysis will be performed on the primary outcome with the following subgroups: adherence group (high adherence: ≥4–5 days per week of adherence), age (≥65 years), asthma overlap, coexisting heart failure, body mass index (>30 kg/), frequent exacerbator (>1 severe exacerbation within 12 months prior to baseline), and treatment with systemic beta-2 antagonist at baseline. A *p*-value of <0.05 will be considered significant.

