### Interim analyses and stopping guidance

A Data and Safety Monitoring Board (DSMB) will be appointed and act according to a charter agreed by the investigators and approved by the sponsor. Six months after the recruitment of the last patient, an interim analysis, based on the ITT population, will be performed to evaluate the continuation of the trial. As main statistical measures, an O’Brien-Fleming plot of the primary endpoint and mortality (calculating *Z*-scores) will be performed. The interim analysis will be performed and presented by a sub-investigator not otherwise involved in the data collection or analyses, overlooked by the trial statistician. The data will be presented in a blinded fashion.

At the interim analysis, the event rate and effect size for the primary endpoint, as well as the safety and progress of the study, will be assessed by the DSMB, and follow-up duration may be adjusted accordingly. Safety will be assessed by comparing event rates to the event rate presumption used for the initial sample size determination. The study may stop for futility if it is deemed improbable to achieve a follow-up duration sufficient to detect a clinically important effect size. The study will not stop for superior efficacy at interim analysis. We wish to prioritize increasing the likelihood of having sufficient power to conclude on the secondary endpoints at the final analysis.

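### The 24 h minimum stay in Table 2 has no exception for death, so an admission cut short by death is a non-event for ICU admission and all-cause hospitalization

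*Protocol article*

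**What the plan says.** Table 2 (Protocol article, Outcomes) defines all-cause hospitalization as "Inpatient, length of stay ≥24 h" and the ICU endpoint as "Inpatient, ICU, length of stay ≥24 h". Neither row, nor the table's footnote, says what happens when death ends the stay before 24 h. All-cause mortality is a separate row of the same table: "Participant registered as dead in the CPR register".

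The primary endpoint is built differently. In the Outcomes text, "The primary efficacy endpoint is the occurrence of hospitalization requiring AECOPD or death from all causes within 12 months". Its hospital component (Table 1, under Explanation for the choice of comparators) is "Inpatient and length of stay ≥24 h, or emergency room visits", so the 24 h rule appears there too, but death is itself an event.

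Under Statistical methods for primary and secondary outcomes, "The primary and all secondary outcomes will be analyzed using the intention-to-treat (ITT) approach", meaning everyone randomized. The primary outcome is shown as a fraction and a relative risk with a 95% confidence interval, and "The same principles will be applied to secondary binomial outcomes".

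**The concern.** A minimum stay is a sensible way to screen out brief, mild contacts. A stay that is short because the patient died is the opposite case, yet the rule treats both alike. A participant who is admitted and dies after 10 hours has no hospitalization on this row; one who survives to 25 hours has one. Both remain in the denominator, so the first is scored as free of the event.

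The endpoint therefore depends partly on surviving the first day. If early deaths were more common in one arm, that arm would lose more events and look better on these two rows. This could hide harm if evening dosing raised early deaths, or understate benefit if it lowered them. ICU admission is likely to be the rarer of the two endpoints, so a few misclassified cases would weigh more there. The article gives its secondary endpoints some importance; on why it will not stop early for efficacy it says "We wish to prioritize increasing the likelihood of having sufficient power to conclude on the secondary endpoints at the final analysis".

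**Working it through.** **The plan's own figures.** The article states no expected rate for either endpoint, so there is no figure to reproduce for this point. Its sample size rests on the primary endpoint only. With p1 = 16,000/178,000 = 8.99% and p2 = p1 × (1 − 0.25 × 0.844) = 7.09%, two-sided alpha 0.05, power 0.80 and a continuity correction, the total is 6,662, as stated. The stay rule in Table 2 does not affect it.

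**Step 1: how one participant is classified.** Take a participant whose only admission in the 12 months ends in death at 10 hours.

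| Endpoint | Rule | Scored as |
|---|---|---|
| Primary composite | Death from all causes counts | Event |
| All-cause mortality | Death in the CPR register | Event |
| All-cause hospitalization | Inpatient stay of at least 24 h | Non-event |
| ICU admission (if in ICU) | ICU inpatient stay of at least 24 h | Non-event |

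If the same participant had another stay of 24 h or more in the period, the last two rows would be events.

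**Step 2: a second gap in the ICU row.** The row does not say whether the 24 h applies to the ICU stay or to the whole hospital stay. For a ward patient moved to ICU on day 3 who dies there after 10 hours, the ICU-stay reading gives a non-event and the hospital-stay reading gives an event.

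**Step 3: events lost (assumed inputs).** About 5,006 per arm (10,013 randomized 1:1, Abstract). Assumptions, not in the article: 1% to 3% truly admitted to ICU, and a share f of 5% to 20% of those lost because their only qualifying-type stay ended in death before 24 h.

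- Lost per arm = 5,006 × ICU rate × f
- Low: 5,006 × 0.01 × 0.05 = 2.5
- High: 5,006 × 0.03 × 0.20 = 30.0

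**Step 4: effect on the relative risk.** With evening over morning, observed RR = true RR × (1 − f_evening)/(1 − f_morning). Setting the true RR to 1.00:

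| f evening | f morning | Observed RR |
|---|---|---|
| 10% | 10% | 1.00 |
| 10% | 5% | 0.90/0.95 = 0.95 |
| 20% | 10% | 0.80/0.90 = 0.89 |
| 10% | 20% | 0.90/0.80 = 1.13 |

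**Step 5: would such a shift be read as an effect?** At an ICU rate of 2% (about 100 true admissions per arm), 20% against 10% gives 80 against 90 counted events. The standard error of log RR is √(1/80 + 1/90 − 2/5,006) = 0.152. The 95% interval is exp(−0.118 ± 1.96 × 0.152) = 0.66 to 1.20, so even this shift would not by itself look like a demonstrated benefit.

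No corresponding range is offered for all-cause hospitalization, because the article gives no rate for it. The formula in step 4 applies with that endpoint's own f.

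**The case against.** The strongest reply is that no death is lost to the trial. Each one counts in the primary composite and in all-cause mortality, which is analysed in the same ITT population. An arm with more rapidly fatal events would show it there. A fixed minimum stay is also a simple prespecified registry definition, and adding fatal short stays makes these rows overlap somewhat with mortality. All of this stands, and it limits the point to two secondary rows.

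A reader might infer that the gravest cases escape the analysis altogether, or that the rule favours the worse arm in this trial. The article supports neither. It gives no ICU rate, no share dying within 24 h and no reason for that share to differ by dosing time. With equal shares the relative risk is unchanged and only events are lost. The remark about power for secondary endpoints in the interim section says nothing about how they are defined.

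It could also be said that such detail belongs in the full protocol or the SAP, which are not shown. That does not answer the point: Table 2 states the rule, and applied as written it gives the classification above.

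**Conclusion.** The point holds for all-cause hospitalization and ICU admission only. As written, a participant whose only qualifying-type stay ends in death before 24 h is a non-event on these rows. The primary endpoint, mortality and the sample size are unaffected.

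Size and direction cannot be derived from the article. Under the assumed rates, about 3 to 30 ICU admissions per arm go uncounted, and a twofold difference in the early-death share (20% against 10%) moves a true relative risk of 1.00 to 0.89 or 1.13. This is a minor defect in two definitions, worth correcting because the correction is nearly free.

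**What to change.** Before outcomes are analysed by arm, amend both rows of Table 2:

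- All-cause hospitalization: *inpatient stay of at least 24 h, or an inpatient stay of any length during which the participant dies*.
- ICU: *ICU stay meeting the 24 h minimum, or an ICU stay of any length during which the participant dies*, with a statement of whether the 24 h refers to the ICU stay or to the hospital stay.
- Identify death during a stay by a CPR death date on or before the registered end date of that stay. A looser marker, such as death on the admission day or the next day, would also catch people discharged alive who die at home.
- Keep the 24 h minimum for stays that end in live discharge.

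The cost is one clause per row and a link between stay dates and the CPR death date, which the mortality endpoint already uses. The downside is a few added events and a small overlap with the mortality endpoint. Deaths in the emergency room without an inpatient stay, and deaths without any admission, remain non-events on these rows; the amendment does not claim to address them.
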